## Abstract

**Background:**

Nursing home residents are at high risk of complications and death due to COVID-19. Lack of resources, both human and material, amplifies the likelihood of contamination in these facilities where a single employee can contaminate dozens of residents and colleagues. Improving the dissemination of and adhesion to infection prevention and control (IPC) guidelines is therefore essential. Serious games have been shown to be effective in developing knowledge and in increasing engagement, and could motivate nursing home employees to change their IPC practices.

**Objective:**

Our aim is to assess the impact of “Escape COVID-19,” a serious game designed to enhance knowledge and application of IPC procedures, on the intention of nursing home employees to change their IPC practices.

**Methods:**

We will carry out a web-based randomized controlled trial following the CONSORT-EHEALTH (Consolidated Standards of Reporting Trials of Electronic and Mobile Health Applications and Online Telehealth) guidelines and incorporating relevant elements of CHERRIES (Checklist for Reporting Results of Internet E-Surveys). Participants will be randomized to either the control or the serious game (intervention) group. First, both groups will be asked to answer a questionnaire designed to gather demographic data and assess baseline knowledge. The control group will then receive a quick reminder of the current national guidelines and links to IPC guidelines for health care professionals, while the other group will play the game. Both groups will then have to answer a second questionnaire designed to assess their willingness to change their IPC practices after having followed their respective material. After completing this questionnaire, they will be granted access to the material presented to the group they were not assigned to and receive a course completion certificate. The primary outcome will be the proportion of participants willing to change their IPC practices according to group. Secondary outcomes will include the analysis of specific questions detailing the exact changes considered by the participants. Factors associated with participant willingness or reluctance to change behavior will also be assessed. Attrition will also be assessed at each stage of the study.

**Results:**

The study protocol has been presented to our regional ethics committee (Req-2020-01262), which issued a declaration of no objection as such projects do not fall within the scope of the Swiss federal law on human research. Data collection began on November 5, 2020, and should be completed by December 4, 2020.

**Conclusions:**

This study should determine whether “Escape COVID-19,” a serious game designed to improve compliance with COVID-19 safe practices, modifies the intention to follow IPC guidelines among nursing home employees.

**International Registered Report Identifier (IRRID):**

DERR1-10.2196/25595

## Introduction

### Background and Importance

Nursing home residents are at high risk of complications and death if they develop symptoms of COVID-19 after being infected with SARS-CoV-2 [1-4]. If infected, a single nursing home employee can potentially contaminate dozens of residents and colleagues [5], since allowing the virus to enter nursing homes leads to rapid interresident transmission [6]. Many long-term care facilities (LTCFs) were ill-prepared to face the first wave of the pandemic and should be helped as much as possible to prevent health care–associated transmission during potential future waves [7]. Such waves seem all the more likely as new COVID-19 cases have been identified since September 2020 in LTCFs located in Geneva, Switzerland, 14 weeks after the last infection was diagnosed here [8]. In addition to aiding efforts to combat the pandemic and to avoid infection, showing a high level of support for nursing home employees may also enhance their motivation [9]. Indeed, since the start of the pandemic, many researchers have pointed out the dramatic lack of resources, both human and material, faced by many LCTFs [10-13].

In nursing homes as in other facilities, viral transmission is often facilitated by the suboptimal application of infection prevention and control (IPC) guidelines [14]. Accordingly, a recent systematic review has identified the promotion of hand and respiratory hygiene and the use of appropriate personal protective equipment to be some of the most critical IPC practices that could help prevent viral transmission among nursing home residents and staff [15]. Dissemination of these guidelines and practices might however be hampered by the current need for physical and social distance [16]. Moreover, application of IPC guidelines may be jeopardized by the presence of divergent and sometimes contradicting messages [17,18], and even by mistrust in guidelines issued by health care authorities [19].

The probability of actually executing an action is strongly linked to the intention of performing it [20]. By increasing engagement and developing knowledge [21,22], serious games could prove instrumental regarding the effective dissemination of IPC guidelines and the promotion of COVID-19 safe practices [23,24]. Using Nicholson’s [25] concept of meaningful gamification, we recently developed “Escape COVID-19,” a serious game specifically designed to motivate health care workers in adopting good IPC practices [26]. Indeed, building and strengthening their intrinsic motivation might be at least as important as reminding them of the most current guidelines to help avoid infection [27]. The usefulness and cost-effectiveness of computer-based serious games is however still debated, and previous studies have pointed out a considerable lack of evidence regarding this education modality [28].

### Objective

Our principal objective is to assess the impact of this serious game on the intention of nursing home personnel to change their IPC practices. We will also aim to determine the factors explaining the reasons that motivate change and those explaining the lack of willingness to change one’s behavior.

## Methods

### Study Design and Setting

We will carry out a web-based, triple-blind (investigator, participants, and data analyst) randomized controlled trial, following the CONSORT-EHEALTH (Consolidated Standards of Reporting Trials of Electronic and Mobile Health Applications and Online Telehealth) guidelines [29]. Elements from CHERRIES (Checklist for Reporting Results of Internet E-Surveys) will be included when relevant [30]. The design and sequence are summarized in Figure 1.

**Figure 1 figure1:**
[figure not shown]
Study design and sequence.

A list of all the nursing homes located in Geneva was obtained through the city’s public health authorities. All staff from these nursing homes will be invited to take part in this study, on a voluntary basis, regardless of their professional status. Information regarding the study and its objectives, including data security, will be provided. Consent will be gathered electronically.

### Online Platform

A specific and fully automated platform created using the latest version of the Joomla content management system [31] and hosted on a Swiss server will be used in this study. All data will be stored on an encrypted, MySQL-compatible database. Only one author ([name]) will be able to access the database. The platform will be secured by the RSFirewall (RSJoomla) [32] and Admin Tools (Akeeba) [33] components. The questionnaires will be administered using Community Surveys Pro (Corejoomla) [34], which allows for the use of branching logic and for the export of responses in CSV format. The Membership Pro (Joomdonation) component will be used to handle registrations [35]. Randomization will be achieved by the GegaByte Random Article module (GegaByte Technologies) [36]. Therefore, randomization will be fully automated, and participants or investigators will not be able to influence group allocation.

Access to the different steps of the study sequence will be managed through Joomla’s native access control list (PHP functions *JUserHelper::addUserToGroup* and *JUserHelper::removeUserFromGroup*). PHP functions will be embedded using Sourcerer (Regular Labs) [37]. Redirect-on-Login (Pages-and-Items) will be used to allow users to immediately access the appropriate section when resuming their study path [38]. Certificates will be generated using RSForm!Pro (RSJoomla) [39]. Daily backups will be scheduled using a cron job script and uploaded on a physically separate server through an encrypted connection.

### First Questionnaire

Participants will be asked to fill in 2 questionnaires. Immediately after activating their account, the first questionnaire will be displayed. This questionnaire is designed to gather demographic data and to assess the initial level of knowledge regarding SARS-CoV-2 transmission and IPC guidelines. To limit attrition, the number of initial questions will be kept at a minimum and branching logic will be used to avoid displaying irrelevant items. The structure of this questionnaire, the original questions in French and their translation in English, are displayed in Multimedia Appendix 1.

### Serious Game

The experiment will be conducted using version 2.1.1 of the “Escape COVID-19” serious game [26], which is freely available on the internet [40]. This serious game has been created under Storyline 3 (Articulate Global) and can be played on many different platforms, including smartphones and tablets, due to its HTML5 compatibility. The game was designed using the SERES framework [41] and Nicholson’s RECIPE (reflection, engagement, choice, information, play, exposition) for meaningful gamification [25]. It is made of 4 different levels representing the typical phases that most health care employees experience daily. To make the game more engaging, the graphics included in the game were designed by [name], a well-known Swiss cartoonist [42].

Throughout the game, players are asked to make choices (Figure 2) or to answer questions directly related to the exposition element (Figure 3), which aims at creating a meaningful narrative in the serious game [25].

Feedback is used extensively [43] to allow the player to correct an answer (Figure 4) and to reinforce the expected behavior (Figures 5-7).

**Figure 2 figure2:**
[figure not shown]
Simple-choice interaction.

**Figure 3 figure3:**
[figure not shown]
The player has to identify the precautions they should take when joining their colleagues for breakfast.

**Figure 4 figure4:**
[figure not shown]
Feedback. The player has submitted an initial answer and is informed that they have selected 3 wrong answers (“3 mauvaises réponses”) and that 2 correct answers are missing (“il vous manque 2 réponses correctes”). They can retry (“Réessayer”) once.

**Figure 5 figure5:**
[figure not shown]
Feedback. The user has correctly answered the question. Visual hints related to the correct answers are displayed (mask, distance arrow, alcohol-based handrub) and a short text emphasizes the expected answers. A thumbs-up image and a plus sign appear, rise, and progressively fade out before the thumbs-up count is updated.

**Figure 6 figure6:**
[figure not shown]
Feedback. The player has retried but has failed to identify the correct answers. Visual hints related to the correct answers are displayed (mask, distance arrow, alcohol-based handrub) and a short text emphasizes the expected answers, which will be displayed when the player clicks on continue (“Continuer”). A virus and a plus sign appear, rise, and progressively fade out before the virus count is updated.

**Figure 7 figure7:**
[figure not shown]
Feedback. When the user has failed to correctly answer the question, the correct answers are displayed with a green background.

Each time the player performs a desirable action or selects the correct answer, a “thumbs up” is awarded. Conversely, the player gets a red virus for each incorrect answer or behavior. If the player accumulates a total of 5 viruses, a game-over screen is displayed (Figure 8). The player can then choose to spend their thumbs up to decrease the virus count (1:1) or to restart the level.

**Figure 8 figure8:**
[figure not shown]
Game-over screen. The player has accumulated 5 viruses and can either spend their thumbs up to decrease the virus count or restart the level.

### Control Materials

The control materials include a quick reminder of the current national guidelines published by the Federal Office of Public Health of the Swiss Confederation [44] and links to IPC guidelines for health care professionals (Vigigerme) provided by the Geneva University Hospitals and freely available on the internet [45].

### Second Questionnaire

The second questionnaire is designed to assess whether the participants intend to change their IPC practices after completing the first set of learning materials (Multimedia Appendix 2). Therefore, the control group will complete it after seeing the standard guidelines, and the serious game group after finishing the game. Once again, branching logic will be used to try to limit attrition.

All multiple-choice and multiple-answer questions are mandatory. A completeness check will be performed at the end of each survey page. Mandatory questions will be highlighted and will have to be answered before allowing participants to move on to the next step. There will be no way to change the answers after completing a page.

### Outcomes

The primary outcome will be the proportion of nursing home employees reporting they are willing to change their IPC practices according to group.

Secondary outcomes will be a composite of the questions based on a 5-point or 6-point Likert scale according to group. Each individual question will also be assessed. We will also aim at identifying the factors associated with participant willingness to change their behavior and analyze the reasons given by participants who are opposed to making changes [46].

We will also assess attrition at each stage of the study according to group [47-50].

### Participants and Sample Size

Health authorities were asked for a comprehensive list of the email addresses of all nursing home employees working in Geneva, to construct a convenience sample. We decided to include all employees, regardless of their professional status or of the potential specificities of the facilities they work in, without any exclusion criteria. To detect a difference of 10% at the .05 significance level with a power of 80%, 388 participants will be needed for each group. The number of eligible employees is estimated to be approximately 4000 people. Therefore, a participation rate of around 20% will be required.

All employees will be invited to participate regardless of their professional status. Participation will be encouraged by delivering a course completion certificate upon completing the study path. No financial incentives will be provided.

To avoid potential duplicates, participants will be required to register on the site using a valid email address. No other personal information, including names, will be asked for during the registration process. The system will automatically send an activation email to check whether the email address provided is valid. Participants will be told that clicking the activation link will be considered as consent to participate in the study.

### Statistical Analysis

Stata 15.1 (StataCorp LLC) will be used for data curation and statistical analysis. Data will be curated by the first author ([name]) and neutral names will be randomly assigned to the control and serious game groups before transferring the DTA file to the blinded data analyst ([name]). To avoid any potential conflicts of interest, the analyst was not part of the serious game development team and did not participate in the original publication describing its development. There will be no interim analysis.

Incomplete answer sets will be excluded. Imputation techniques will not be used. Answer sets marked as completed should not contain any missing value by virtue of the completeness checks automatically performed by the survey component.

Univariate and multivariable logistic regression will be used to assess the primary outcome. Adjustment will be done according to prior knowledge (expressed as percentage of correct answers), professional status, and nursing home. The expected sample size should prevent overfitting. We will check the log-linearity assumption graphically and test the goodness of fit using the Hosmer-Lemeshow test.

The analysis of secondary outcomes will be carried out by assigning numerical values to the answers gathered through the use of Likert scales. As the 6-point Likert scale ranges from 1 (not at all) to 6 (very much), the same numbers (ie, a score ranging from 1 to 6) will be used for each item. The composite outcome will be the sum of the 9 questions and will be analyzed using univariate and multivariable linear regression analyses, with the same adjustment variables as the primary outcome. Each question will be analyzed separately.

For the 5-point Likert scale, values ranging from –2 to +2 will be assigned to each answer, with positive values attributed to changes enhancing IPC behavior. A composite outcome will be generated, which will be the sum of these values. We made the choice to treat this discrete variable as continuous and use a linear regression analysis, first univariate, then multivariable (with the same adjustment variables as the primary outcome). The same weight will be applied to all questions when computing composite outcomes. As a reduction in the use of N95 respirator masks can also be considered as enhancement depending on the setting, a sensitivity analysis will be done by analyzing the composite outcome with and without the N95 respirator mask item.

Descriptive statistics will be used to detail the factors associated with participant willingness to change or refuse to change behavior. The Student *t* test and the chi-square test will be used to assess differences between groups.

The curated data file will be made available on the Mendeley Data repository.

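### The primary analysis keeps only complete answer sets, although reaching the outcome questionnaire asks more of the game arm; no sensitivity analysis for missing outcomes is stated

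*Protocol article*

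**What the plan says.** All references are to the protocol article.

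- **Statistical Analysis** fixes the rule: "Incomplete answer sets will be excluded. Imputation techniques will not be used". The primary outcome is then analysed by logistic regression, crude and adjusted for prior knowledge, professional status and nursing home. The only sensitivity analysis named concerns the N95 item in a secondary composite.
- **Second Questionnaire** sets when the outcome is measured: "the control group will complete it after seeing the standard guidelines, and the serious game group after finishing the game".
- **Serious Game** describes four levels and a game-over screen at five viruses, after which the player spends points or restarts the level. **Control Materials** describes a quick reminder of national guidelines plus links.
- **Outcomes** adds: "We will also assess attrition at each stage of the study according to group". No consequence for the primary estimate is attached to this.
- **Main Considerations** (Discussion) expects that some staff may not take to a game, and connects this with resistance to change. **Limitations** says the game may suit some profiles better than others. It discusses low participation, but not drop-out after allocation.
- **Participants and Sample Size** states: "To detect a difference of 10% at the .05 significance level with a power of 80%, 388 participants will be needed for each group".

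**The concern.** Randomisation protects a comparison of everyone allocated. Here the comparison is restricted to those who reached the end, and the route to the end differs by arm. Someone who dislikes the game can leave before the outcome is asked. Someone in the control arm has less to get through.

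The outcome is willingness to change, and the article itself links dislike of the game with resistance to change. A connection between dropping out and the unobserved answer is therefore plausible. If it exists and is stronger in one arm, part or all of an observed difference could be selection rather than an effect of the game.

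The safeguards in the article do not settle this:

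- The completeness checks prevent gaps within finished questionnaires; they do not prevent abandonment.
- Adjustment for knowledge, profession and home does not capture attitude to the game.
- Blinding the analyst does not change who is in the data file.
- Counting attrition by group would reveal an imbalance but leaves the estimate as it is.

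**Working it through.** **1. The plan's own figure.** Inputs: two-sided 5% level, 80% power, a 10-point difference, equal arms. The baseline rate is not stated; 50% versus 60% is assumed.

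n = [1.96 × √(2 × 0.55 × 0.45) + 0.842 × √(0.50 × 0.50 + 0.60 × 0.40)]² / 0.10² = 387.3, rounded up to 388. This reproduces the stated size.

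Two arms give 776, and 776/4000 = 19.4%, which matches "Therefore, a participation rate of around 20% will be required". So the calculation holds no allowance for drop-out, and the article implies no completion rate. Every completion rate below is an assumption.

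**2. False difference with no true effect.** Let true willingness be 50% in both arms, c the completion rate in an arm, and d the willingness among its drop-outs. Willingness among completers is (0.5 − (1 − c) × d) / c.

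Control c = 90%, game c = 70%:

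- d = 30%: control (0.5 − 0.03)/0.9 = 52.2%; game (0.5 − 0.09)/0.7 = 58.6%; difference **+6.3 points**.
- d = 20%: control (0.5 − 0.02)/0.9 = 53.3%; game (0.5 − 0.06)/0.7 = 62.9%; difference **+9.5 points**.
- d = 50% (drop-out unrelated to willingness): 50% in both arms; difference **0**.
- d = 70% to 80% (relation reversed): **−6.3 to −9.5 points**.

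With game completion of 80% instead, d = 30% gives 55.0% − 52.2% = +2.8 points and d = 20% gives 57.5% − 53.3% = +4.2 points.

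**3. False-positive rate.** Take 388 completers per arm and a two-sided pooled z test. The rejection probability is about Φ((difference − 1.96 × SE₀)/SE₁), where SE₀ is the pooled and SE₁ the unpooled standard error.

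- +6.3 points: (0.0635 − 1.96 × 0.0357)/0.0356 = −0.18, so about **43%**.
- +9.5 points: (0.0952 − 1.96 × 0.0354)/0.0353 = 0.73, so about **77%**.

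Splitting 776 completers in proportion to completion (436.5 and 339.5) changes these to 42% and 76%.

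**4. What the scenario implies.** In the game arm, d = 30% means 41/50 = 82% of willing and 29/50 = 58% of unwilling staff finish. With d = 20% the figures are 44/50 = 88% and 26/50 = 52%.

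**5. A second parameterisation.** Let control drop-out be unrelated to willingness. In the game arm let 90% of willing and 60% of unwilling staff finish. The observed game rate is 0.45/(0.45 + 0.30) = 60%. That is a false +10 points, the whole target difference, and the test rejects about 80% of the time. At 70% true willingness the same completion gives 0.63/(0.63 + 0.18) = 77.8%, or +7.8 points. Reversed dependence (60% of willing, 80% of unwilling finishing) at 50% gives 0.30/0.70 = 42.9%, or −7.1 points.

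**6. What bounds would look like.** Suppose completers show 60% (game) versus 50% (control), with completion 70% and 90%.

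- All missing counted as not willing: 0.60 × 0.70 = 42% versus 0.50 × 0.90 = 45%, −3 points.
- Worst case for the game: 42% versus 45% + 10% = 55%, −13 points.
- Best case for the game: 42% + 30% = 72% versus 45%, +27 points.

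**The case against.** The strongest reply is that nothing in the article shows the bias will occur. Unequal completion alone does no harm, as the zero line in the working shows. The outcome is willingness to *change*, not motivation: staff who already comply may finish the game and report no intended change, which could push the bias the other way. A reader might infer that the design must favour the game. The documents do not support that, because they give neither completion rates nor any relation between drop-out and willingness.

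Several features may also hold drop-out down. Participants can resume where they stopped, the certificate comes only after the study path is completed, a game-over can be bought off with points, and the whole path is put at about 30 minutes. These may narrow the gap between arms, but they do not remove the difference in what must be finished.

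Two further inferences are tempting and should not be drawn. One is that the rule discards willingness answers already given by people who left later. The article says only that pages lock ("There will be no way to change the answers after completing a page"). Where the willingness item sits is in Multimedia Appendix 2, which is not shown. The other is that most drop-outs will have completed the first questionnaire; nothing says so.

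Nor is imputation from knowledge, profession and home a real remedy. The adjusted model already contains these variables, and they do not measure attitude to the game.

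What survives is narrower. The article itself fixes exclusion without imputation, so this is not a detail left to another document, and it states no check on how much the primary result depends on that rule.

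**Conclusion.** The concern holds as a conditional one. A completer-only comparison with arm-specific burden before the outcome is open to selection bias after randomisation, and the article states no sensitivity analysis that would show whether a result withstands it. Under the assumed 50% willingness, 90%/70% completion and 20-30% willingness among drop-outs, the false difference is 6.3 to 9.5 points, against a target of 10. With 80% game completion it is 2.8 to 4.2 points. It is zero without a link between drop-out and willingness, and negative if the link reverses. The direction is therefore uncertain; favouring the game is plausible, not shown. Attrition by group will show whether completion differs, but not whether it is related to willingness.

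**What to change.** Keep the completer analysis as planned. Before unmasking, pre-state for the primary outcome:

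1. A sensitivity analysis of all randomised participants from accredited homes, using any willingness answer that was recorded.
2. Best-case and worst-case bounds, or a range of arm-specific assumptions for missing outcomes, with non-completers counted as not willing as one scenario among them.
3. Attrition by arm reported beside these results.
4. A statement that the conclusion about the game will be limited if the result is not robust across plausible scenarios.

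The questionnaires and study design, which Limitations says cannot change, are untouched. The cost is a few extra model runs and possibly wide bounds (−13 to +27 points in the example).

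Counting non-completers as not willing should neither stand alone nor serve as a strict gate, because it can itself bias against the arm with more drop-out. With 50% willingness in both arms and drop-out unrelated to it, completion of 90% and 70% gives 45% versus 35%, a false 10-point disadvantage for the game. Requiring that scenario to agree with the completer result would also block a true 60% versus 50%, which would appear as 42% versus 45%.
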